## Abstract

**Background:**

Parkinson’s disease (PD) is a common degenerative neurological disorder that causes loss of independence and decreased quality of life. The prevalence of PD tends to increase with age. In China, the morbidity rate of PD among people aged more than 65 years old is 1.70%. As an important component of traditional Chinese *Qigong* exercises, Tai Chi is a popular and safe exercise, especially for older adults in China. And it may result in promising gains for PD patients. However, current evidence is insufficient to inform the use of Tai Chi in the management of PD. Therefore, the aim of this trial is to systematically evaluate the effect of Tai Chi on PD and determine whether Tai Chi is an eligible exercise program for Chinese PD patients.

**Methods/Design:**

A single-blind, parallel randomized controlled trial will be conducted. One hundred and forty-two patients with PD will be randomly assigned to a Tai Chi group (n = 71) or routine exercise group (n = 71). Subjects will participate in supervised study programs 3 times per week for 2 months and will be followed for an additional 6 months after formal training stops. The primary outcome measures include Berg Balance Scale, Timed Up and Go Test and Six-Minute Walk Test, which are known to be valid and reliable clinical instruments. The Unified Parkinson’s Disease Rating Scale Motor Section and Parkinson’s Disease Questionnaire-39 will be used as the secondary outcome measure. All outcomes will be measured at baseline, 2 and 8 months. The sample for this trial (N = 142) will provide relevant information to detect the improvement of balance, gait and quality of life in either of the 2 exercise groups.

**Discussion:**

Findings from this study will provide insights into the effects of Tai Chi in people with PD. The information gained from this project has the potential to influence the clinical decisions of Chinese doctors, and will provide clear evidence as to whether Tai Chi should be advocated in people with PD.

**Trial registration:**

The trial was registered at (ChiCTR-TRC-14004549) on 22 April 2014.

## Background

Parkinson’s disease (PD) is a common neurodegenerative disorder that is associated with four landmark symptoms of resting tremor, bradykinesis, rigidity and decreased postural reflexes [1]. Globally, there are at least 4 million people estimated to be diagnosed with PD [2]. Although the specific causes of PD are unknown, incidence increases with age, especially after 50 years old [3]. In China, PD prevalence is 1.70% in people aged more than 65 years old [4]. It is reported that in people with PD it is common to develop a slow, shuffling and dysrhythmic gait [5]. Also, most people with PD will ultimately develop impaired balance [6]. Despite advances in medical care, gait disturbance and balance decrements worsen as the disease progresses, contributing to loss of independence, falls and poor quality of life [7]. Therefore, people with PD gradually place a strain on societies, healthcare and financial systems.

Exercise, as one of non-pharmacological interventions in assisting the treatment of PD, has demonstrated efficacy in improving gait disturbance, balance decrements and frequency of falls in patients with PD [8-10]. It may improve brain health by suppressing oxidative stress, stabilizing calcium homeostasis and plasticity-related changes in the central nervous system including enhanced glucose utilization, synaptogenesis, angiogenesis and neurogenesis [11-14]. Also, there is supporting evidence indicating that intensive exercise is more effective in controlling balance and gait for PD in relevant studies [15]. However, the prevalence of older Chinese people using such exercises is quite low. As an important component of traditional Chinese *Qigong* exercises, Tai Chi is an ancient art and science of healthcare that is quite popular with Chinese older adults.

Tai Chi, as a mind-body exercise, consists of a series of dance-like movements linked in a continuous sequence, flowing slowly and smoothly from one movement to another that emphasizes weight transfer and movement of the body [16]. By doing so, it may improve postural control that can also benefit balance, gait and quality of life and some studies have demonstrated the beneficial effects of Tai Chi in improving gait and balance [16-18]. The last systematic review concluded that Tai Chi resulted in promising gains in mobility and balance among PD patients, but they were significantly limited due to small sample size, short follow-up period, poor methodological quality and heterogeneity in population characteristics with few Chinese PD patients being included [19,20]. Thus, new and high-quality randomized controlled trials are warranted to prove the previous findings, especially for Chinese PD patients.

The aim of this randomized controlled trial is to systematically evaluate the effect of Tai Chi in improving gait, balance and quality of life in patients with PD in China by observing the difference between the Tai Chi group and routine exercise group. The hypothesis is that patients with PD who are treated with Tai Chi will experience a greater reduction in Parkinsonian symptoms as well as improved gait, balance and quality of life in comparison with those treated with routine exercise.

## Methods and Design

### Trial design

A single-blind (assessors), parallel randomized controlled trial will be conducted to compare Tai Chi with routine exercise (allocation ratio 1:1). The study period is 8 months including a 2-month supervised intervention and a 6-month follow-up with the primary outcome measured at baseline, 2 and 8 months. The primary site for conduct of the study, including all study visits and Tai Chi interventions will be conducted at the Affiliated Hospital of Jining Medical University, Jining, Shandong, China. Routine exercise will be conducted in a home-based environment.

### Participants and recruitment

People attending Medicine for the Elderly or Neurology outpatient appointments at Affiliated Hospital of Jining Medical University, Jining, Shandong, China, for diagnosed or probable PD will be invited to participate in the study.

### Inclusion criteria

Adults diagnosed with, or with probable idiopathic, PD with a disease severity rating of stage 1 to 4 on the Hoehn and Yahr scale (which ranges from 1 to 5, with higher scores indicating more severe disease) [21].Prescribed one or more anti-parkinsonian medications by a consultant neurologist or consultant physician with specialist knowledge of neurological disorders.Chinese speaking and literate (participants are required to actively engage in the therapy process).Stable medication use; that is, not altered within the previous month and not expected to change during the period of the research project (8 months).Without dementia or significant cognitive impairment. The clinical team will judge whether the patient has the cognitive capacity required to participate in the trial; that is, has read patient information, complete self-report questionnaires and engaged actively in the intervention process.Willing to be assigned to any of the two interventions.

### Exclusion criteria

Suspected Parkinsonism due to causes other than idiopathic PD.Current participation in any other behavioral or pharmacologic study or instructor-led exercise programs.Participation of a structured exercise program in the preceding 2 months.Unavailability during the period of the study.

### Recruitment

Based on inclusion criteria 1, 2, 3, 4 and 5, participant identification will be performed by the clinical team 2 weeks prior to upcoming outpatient appointments. An information package containing: a patient invitation letter, participant information sheet, and a consent form will be posted out to potentially eligible participants. The patient information will be supplemented by an information sheet for the spouse/carer. Patients will be required to return the participant information sheet and the accompanying consent form. Patients who did not return the materials will be contacted by telephone to discuss their suitability for participation. Patients who are willing to participate but do not meet eligibility criteria will be thanked for their interest. Eligible patients will be approached for their consent to participate in the trial on the day they attend clinic for their outpatient appointment. If the consent is obtained, the patient would be recruited and the whole recruitment will be achieved by a 10- to 12-month rolling program (Figure 1).

**Figure 1 Fig1:**
[figure not shown]
**Study design, recruitment, randomization to treatment, and outcomes assessment.** PD: Parkinson’s disease.

### Randomization

After completing the baseline test, each participant will learn his/her group assignment by receiving a sealed, sequentially-numbered envelope from the project director and opening the envelope that contains the group assignment randomly assigned to his/her sequence number. The sequence numbers are generated by using Statistical Package for the Social Sciences (SPSS) 18.0 statistical software (SPSS Inc., Chicago, IL, USA). Measurement technicians who are responsible for data collection are blinded to participant group assignment.

### Outcome measures

#### Primary outcome measures

All participants will be measured before commencing each intervention (pre-test) and upon completion (post-test). The primary outcome measure includes the Berg Balance Scale (BBS), Timed Up and Go Test (TUG) and Six-Minute Walk Test (6MWT), which are known to be valid and reliable clinical instruments [22]. According to the wide disability spectrum associated with PD, balance impairments are common in patients [23]. The BBS will be utilized to identify potential training effects on balance [24]. Functional gait performance will be measured by the TUG [25]. Participants will be asked to walk as quickly as they safely can under all conditions and will be permitted to use their usual gait aid. The TUG measures a participant’s ability to perform sequential gait movements and has been proved to be a reliable outcome measure for use in PD. In addition, the 6MWT will be completed to quantify walking capacity, measured as the distance covered in which conducted on a 20-meter walkway next to the laboratory and we record total distance traveled. This test has demonstrated high reliability in people with PD [26]. Assessment will be performed during the patient’s self-reported optimal ‘ON’ period, often 1 hour after medication.

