#### Secondary outcome measures

The Unified Parkinson’s Disease Rating Scale Motor Section (UPDRS-III) [27] and the Parkinson’s Disease Questionnaire-39 (PDQ-39) will be used as the secondary outcome measures. The UPDRS-III will be administered by a trained clinician who is blinded to group assignment. Health-related quality of life will be measured using the PDQ-39, a generic health-related quality of life measure, which is specific to the PD population [28]. Participants will also be assessed at peak dose (approximately 1 hour post administration) of anti-Parkinsonian medication. Several measures will be taken to characterize participants at each assessment session. Severity of PD will be categorized with the Hoehn and Yahr scale [21] and freezing will be characterized by the Freezing of Gait Questionnaire [29], confidence will be measured by the Ambulatory Self-confidence Questionnaire [30]. General demographic information to be recorded will be: age, disease duration, medical history, mobility aid use, medication type and dosage, and so on. Medication will be documented in detail at every assessment time point.

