### Efficacy analysis of outcome measures

The primary analysis will compare the changes on BBS from baseline to endpoint of treatment between two treatment groups using analysis of covariance (ANCOVA) adjusting by the BBS baseline value. The statistically significant level of *P*-value is less than 0.05. If any participants drop out from the trial, intention-to-treat analyses will be adopted. Participants who withdraw will be treated as having no change from baseline at all times after dropping out. In addition to intention-to-treat analyses, multiple imputation will be used to perform secondary analyses. We will also check the mechanism of the participation drop-out and determine whether the missing data is ignorable or not. If non-ignorable missing data methods are needed, we will explore both selection and pattern-mixture types. All efficacy analyses of primary and secondary outcome measurements will be conducted by the same analytical strategy.

All participants will undergo sub-group analysis test for potential effect modification for the presence of a spouse/carer on the therapeutic effect. Appropriate adjustments will be made in the statistical analyses for potential factors which are unevenly distributed between the two groups. Participants with significantly impairment of balance, gait and quality of life at baseline will be analyzed to determine the independent impact of these disturbances on the therapeutic effect. Adjusted estimates will be obtained by identifying baseline imbalances and incorporating them into a regression model by pre- and post-intervention primary outcome scores. If normal distribution assumptions were not met, non-parametric analysis will be adopted even after suitable transformations.

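### Three outcomes are declared primary, but the primary analysis is BBS alone and the same P < 0.05 analysis covers every outcome, so the plan does not settle which result decides the trial

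*Protocol article*

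**What the plan says.** The protocol article labels outcomes in one way and analyses them in another.

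- **Labels.** The abstract (Methods/Design) says: "The primary outcome measures include Berg Balance Scale, Timed Up and Go Test and Six-Minute Walk Test". The section Primary outcome measures lists the same three, without ranking them: "The primary outcome measure includes the Berg Balance Scale (BBS), Timed Up and Go Test (TUG) and Six-Minute Walk Test (6MWT"). The next section gives the other label to two further instruments, UPDRS-III and PDQ-39: "the Parkinson’s Disease Questionnaire-39 (PDQ-39) will be used as the secondary outcome measures".
- **Analysis.** Efficacy analysis of outcome measures says: "The primary analysis will compare the changes on BBS from baseline to endpoint of treatment between two treatment groups", by ANCOVA adjusted for baseline BBS. The threshold follows: "The statistically significant level of *P*-value is less than 0.05". The same paragraph ends: "All efficacy analyses of primary and secondary outcome measurements will be conducted by the same analytical strategy".
- **Sample size.** A difference of 4.0 and a standard deviation of 7.2 are given for BBS. An earlier study's TUG result, with 65 per group, is also cited before the total of 142 is reached. No difference or standard deviation is given for TUG or 6MWT.
- **Timing.** Trial design describes follow-up "with the primary outcome measured at baseline, 2 and 8 months".

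**The concern.** The outcome sections and the efficacy section give different answers to the question of which result makes this a positive trial. On the labels, TUG and 6MWT are primary outcomes. On the primary analysis, only BBS is. The article does not say which prevails, and the instruction to analyse all outcomes in the same way lets TUG and 6MWT keep their primary label with an unadjusted test.

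The case that matters is a null BBS with a significant TUG or 6MWT. An author could report that as a positive primary result and point to the abstract and the outcome section in support. The 5% error rate attached to the BBS test would not apply to that claim. The Discussion expects the findings to provide clear evidence on whether Tai Chi should be advocated in Parkinson's disease, so the reader needs to know in advance which result carries that conclusion.

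**Working it through.** **Inputs**
- Outcomes labelled primary: 3 (abstract; Primary outcome measures).
- Significance level: 0.05 (Efficacy analysis), two-sided (Sample size).
- BBS difference 4.0, SD 7.2, 71 per group, 20% drop-out (Sample size).
- Correlation between the three test statistics: not in the document. Values of 0.3, 0.5 and 0.7, equal for all pairs, are assumed.

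**Step 1. The plan's own figure.** The required total for BBS is stated as 116. The normal formula gives n per group = 2(1.960 + 0.842)² × 7.2² / 4.0² = 50.9, so 51 per group and 102 in total (104 with the t distribution). The stated 116 is not reproduced. That is a separate matter: nothing below uses 116.

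**Step 2. Error if any one of the three at T1 counts as success.** Under independence, the two-sided family-wise error is 1 − 0.95³ = 0.143. For rejections favouring Tai Chi only, each test has a 2.5% chance, and 1 − 0.975³ = 0.073. For correlated outcomes, the same probabilities were obtained by numerical integration over three equally correlated normal test statistics with critical value 1.960.

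| Assumed correlation | Any rejection, either direction | Any rejection favouring Tai Chi |
|---|---|---|
| 0 | 14.3% | 7.3% |
| 0.3 | 13.6% | 6.8% |
| 0.5 | 12.5% | 6.3% |
| 0.7 | 10.9% | 5.5% |
| Nominal, one test | 5.0% | 2.5% |

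**Step 3. BBS power under the two main ways of repairing this.** Evaluable patients: 71 × 0.8 = 56.8, about 57 per group. The standardised difference is 4.0 / 7.2 = 0.556, and the expected test statistic is 0.556 × √(57/2) = 2.97.
- BBS as sole primary at 0.05: power = Φ(2.97 − 1.96) = 84% (84% also with the t distribution).
- Three primaries with a Bonferroni split, 0.05/3 = 0.0167: power = Φ(2.97 − 2.39) = 72% (70% with the t distribution). Restoring 80% would take 68 evaluable per group, or 68 / 0.8 = 85 per group and 170 randomised.

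**Step 4. If all three had to be significant.** No adjustment of the significance level would be needed, but power cannot be computed, because the document gives no difference or SD for TUG or 6MWT.

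**The case against.** The strongest reply is that a single confirmatory test is already named. The efficacy section calls one comparison the primary analysis, fixes its contrast at the end of treatment and its threshold at 0.05, and the only difference and SD in the sample size belong to BBS. On that reading the primary test holds 5%. A multiplicity rule for the remaining outcomes could properly sit in a statistical analysis plan that is not shown, so its absence here is not an error. Both observations are right as far as they go. What they do not remove is the conflict in labels. The article separates primary from secondary instruments on purpose and puts TUG and 6MWT on the primary side, and an analysis plan could not agree with both sections.

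Two stronger readings are tempting and are not supported.
- A reader might infer that the plan adopts success on any one of three. No section states such a rule. The text permits the claim; it does not prescribe it.
- A reader might count six primary tests, because Trial design has the primary outcome measured at 2 and 8 months. That sentence is a measurement schedule, in line with Table 1, and the efficacy section fixes the primary contrast at end of treatment. Error rates for six tests therefore do not apply.

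It is also fair to say that the two-sided rates count rejections in either direction. For the claim that Tai Chi is better, the right-hand column of the table is the relevant one. Nor would it be exact to say that the sample size rests on BBS alone, since an earlier TUG result is cited there too. That citation makes the status of TUG less clear, not clearer.

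**Conclusion.** The point holds as a contradiction within the document about what is primary, with a consequence for what may be claimed. The BBS analysis taken by itself is sound at 5%. If TUG or 6MWT could also carry the primary claim at T1, the false-positive rate in favour of Tai Chi would be about 5.5% to 7.3% instead of 2.5%, an excess of about 3 to 5 percentage points. The corresponding two-sided rate would be about 11% to 14% instead of 5%. These ranges assume that success on any one outcome is accepted and that correlations lie between 0 and 0.7. The document gives no correlations. The contradiction itself depends on none of these assumptions and should be resolved before outcome data are seen.

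**What to change.** **Change**
- Name BBS change from baseline to T1 (2 months) as the single primary outcome, tested at two-sided 0.05, as the efficacy section already does.
- Make TUG and 6MWT at T1 key secondary outcomes, tested at 0.05 only if BBS is significant, in an order fixed before outcome data are seen. TUG then 6MWT is one option; the document itself gives no order. This holds the family-wise error at 5% over the three.
- Report the 8-month results, UPDRS-III and PDQ-39 as secondary, with confidence intervals.
- Align the abstract and Primary outcome measures, and state in Trial design that T1 is the primary time point.

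Keeping three primary outcomes with an adjustment, or requiring all three, would also remove the contradiction. The first lowers BBS power to about 70%, and the second has a power that the document does not allow anyone to compute.

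**Cost.** No extra patients are needed, and BBS power stays at about 84% with 57 evaluable per group. TUG and 6MWT can no longer carry the primary claim alone. Trial status says recruitment is ongoing and the trial is registered, so this changes the declared primary outcomes of a running trial. It needs a dated amendment and a registry update, made without sight of outcome data.

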#### Secondary outcome measures

The Unified Parkinson’s Disease Rating Scale Motor Section (UPDRS-III) [27] and the Parkinson’s Disease Questionnaire-39 (PDQ-39) will be used as the secondary outcome measures. The UPDRS-III will be administered by a trained clinician who is blinded to group assignment. Health-related quality of life will be measured using the PDQ-39, a generic health-related quality of life measure, which is specific to the PD population [28]. Participants will also be assessed at peak dose (approximately 1 hour post administration) of anti-Parkinsonian medication. Several measures will be taken to characterize participants at each assessment session. Severity of PD will be categorized with the Hoehn and Yahr scale [21] and freezing will be characterized by the Freezing of Gait Questionnaire [29], confidence will be measured by the Ambulatory Self-confidence Questionnaire [30]. General demographic information to be recorded will be: age, disease duration, medical history, mobility aid use, medication type and dosage, and so on. Medication will be documented in detail at every assessment time point.

### Intervention

#### Tai Chi

The intervention will be composed of 1-hour group Tai Chi classes customized for patients with PD, and held 3 times weekly for 2 months. The program will include traditional warm-up exercises, followed by 6 simplified Tai Chi movements taught by 2 certified and experienced instructors (average experience of 20 years). Warm-up exercises (15 minutes) will include weight-shifting, arm-swinging, gentle stretches of the neck, shoulders, spine, arms, legs, visualization techniques, and traditional breathing methods (that is whole-body breathing). These exercises will help release tension in the physical body, incorporate mindfulness and imagery into movement, increase awareness of breathing, and promote overall relaxation of body and mind. The core Tai Chi movements (45 minutes) will be adapted from the Yang Short-form style of Master Cheng Man-ching [16], and performed repetitively. The six movements are as follows: (1) wave hands like clouds; (2) part the wild horse’s mane on both sides; (3) step up and thrust downward; (4) strike to ears with both fists; (5) repulse monkey; (6) grasp sparrow’s tail. These movements were selected because they are easy to comprehend and emphasize repeated bilateral stepping with body-weight transfer that is helpful to retain postural stability for PD patients. Chairs will be provided for resting, and patients will be allowed to progress at their own comfort and pace. After 2 months of training, the Tai Chi group will be provided with a 30-minute instructional videotape that outlines the exercises presented in class. Patients will be required to continue to practice at home at least three times per week. Class attendance will be monitored, and adherence to practice will be tracked via self-report logs, which obtain the weekly frequency and duration of home Tai Chi practice.

